### Preparing and assisting data collection in the practices

The methodology of the study was developed in close exchange with the psychiatric practices of the management association providing AO. To make this pragmatic trial
[26] work, we sought to adjust our study design as closely as possible to the conditions and requirements of daily life and work in the psychiatric practices. Further, all practices are visited by a member of the research team for recruitment and for explaining the study. This team member then becomes the personal contact for this practice throughout the study. The team member trains the practice assistant in handing out and collecting the study materials to patients receiving the intervention and to controls. During recruitment and assessment times the study-team member holds weekly telephone contact to its assigned practice. A telephone hotline is implemented for upcoming urgent questions concerning the study.

### Sample size

Previous studies performed in Leipzig, Germany, have shown a mean number of days spent in psychiatric inpatient care by schizophrenic patients of 47 (SD 83)
[27]. Further, studies estimated the mean decrease of inpatient days that can be expected from interventions to be 40%
[28]. According to Hedeker and colleagues (1999), a baseline sample size of 242 participants in each group would be required to detect a small effect size of 0.2 with a power of 0.80 at a two-tailed significance level of 0.05
[29].

Previous studies have shown that 20% of patients cannot be traced for follow-up or do not return questionnaires over a 12-month survey period
[27].We aim to reduce drop-out numbers by keeping records of patients' telephone contact details as well as secondary contact names and addresses at the practices of the attending psychiatrists. If patients fail to return for assessment to the attending practice, they are contacted by phone and asked whether they want to continue with the study. This way, we hope to keep the number of drop-outs at a rate of 10%. Thus, the total number of participants to be initially recruited will be 268 patients per group or 536 in total.

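### The 242 per group does not follow from the printed inputs, and on the scale of the quoted inpatient days it gives 80% power for about a 45% reduction rather than the assumed 40%

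*Protocol article*

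**What the plan says.** The Sample size section gives three planning facts and one result.

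- Planning level: "a mean number of days spent in psychiatric inpatient care by schizophrenic patients of 47 (SD 83"), from previous studies. The reference period is not given.
- Expected effect: previous studies put "the mean decrease of inpatient days that can be expected from interventions to be 40" per cent.
- Result, credited to a published sample-size method: "a baseline sample size of 242 participants in each group would be required to detect a small effect size of 0.2". Power is set at 80% and the test is two-sided at the 5% level.
- Attrition: "Previous studies have shown that 20% of patients cannot be traced for follow-up or do not return questionnaires over a 12-month survey period". With the retention measures described, the authors hope for 10% and recruit 268 per group, 536 in total.

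Elsewhere in Methods, inpatient days come from the CSSRI, which looks back three months and is completed five times, at t0 and then quarterly (Outcome and process parameters). The Statistical analysis section plans repeated-measures, random-effects or GEE models. It makes adjustment for baseline differences conditional on whether it appears to be needed.

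**The concern.** The paragraph states an effect size, a power, a significance level and a number per group, and these four do not agree for a plain two-group comparison. Nor does the text say how 0.2 relates to the 47 days, the SD of 83 and the 40% reduction beside it. The 40% reduction corresponds to 0.227 if the SD is common.

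Inpatient days are main hypothesis II. The Conclusion of the article expects the findings to be useful whichever way they fall. A null result will therefore be read against the claimed 80% power, so the reader must know which difference, on which scale, that 80% refers to.

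**Working it through.** **Inputs from the documents.** Effect size 0.2; power 0.80; two-sided alpha 0.05; 242 per group; mean 47, SD 83; reduction 40%; 1:1 recruitment; 268 recruited per group; 20% loss in previous studies. **Not in the documents:** the within-patient correlation, the number of occasions used for 242, the SD in the intervention group and the reference period of the 47 days. These are treated as assumptions below.

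**1. Attempt to reproduce 242 as a two-group comparison.** By the normal approximation, n = 2(1.960 + 0.842)² / d². With d = 0.2 this is 392.4; with the t distribution it is 393.4, so 394 per group. At 242 per group the power for d = 0.2 is 59%. The stated 242 is not reproduced.

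**2. Using the paragraph's own planning figures.** 0.40 × 47 = 18.8 days; with a common SD, 18.8 / 83 = 0.2265. The t-based n is 306.9, so 307 per group. At 242 the power is 70%.

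**3. What does give 242.** For the mean of T occasions with common correlation ρ, n = 392.4 × [1 + (T − 1)ρ] / T. Setting n = 242 gives:

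| Occasions T | ρ needed |
|---|---|
| 2 | 0.23 |
| 3 | 0.42 |
| 4 | 0.49 |

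With four quarters and an assumed ρ = 0.5, n is about 246 and power at 242 is about 79%. At ρ = 0.4 power is 84%; at ρ = 0.8 it is about 66%. So 242 is consistent with 0.2 as a per-quarter effect and ρ of about 0.5 or less.

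**4. Scale of the quoted 47 (SD 83).** Days counted within a window of L days lie between 0 and L. With mean 47 the SD cannot exceed √[47(L − 47)]:

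- L = 91: √(47 × 44) = 45.5
- L = 182.5: √(47 × 135.5) = 79.8
- SD 83 requires L ≥ 47 + 83²/47 = 193.6

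The planning figure therefore cannot describe a quarter or a half-year. It is a total over a longer window.

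**5. What 242 means on that total.** The mean of the quarterly counts is the total divided by a constant, so both give the same test. A per-quarter effect of 0.2 with ρ = 0.49 over four quarters is 0.2 × √[4 / (1 + 3 × 0.49)] = 0.255 SD of the total; T = 2 and T = 3 with their ρ give the same value. Solving the two-group power directly for 80% at n = 242 also gives d = 0.255. In days: 0.255 × 83 = 21.2, and 21.2 / 47 = 45%.

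**6. Power for the assumed 40% (18.8 days), by SD assumption.** The intervention mean would be 28.2 days. For 20% loss, 268 × 0.8 = 214 per group.

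| Intervention-group SD | Pooled SD | d | Power, n = 242 | Power, n = 214 |
|---|---|---|---|---|
| 83 (common) | 83 | 0.227 | 70% | 65% |
| 83 × √0.6 = 64.3 (variance scales with mean) | √[(83² + 64.3²)/2] = 74.2 | 0.253 | 79% | 74% |
| 83 × 0.6 = 49.8 (SD scales with mean) | √[(83² + 49.8²)/2] = 68.4 | 0.275 | 85% | 81% |

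**7. Gain from baseline adjustment.** Adjusting for a baseline covariate with correlation r multiplies n by about (1 − r²). For the 40% effect with common SD, 306.9 × (1 − r²) = 242 gives r = 0.46.

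**The case against.** The strongest reply is that the paragraph never describes a single two-group comparison. It credits 242 to a separate method, service use is assessed quarterly, and repeated-measures models are planned. A correlation near 0.5 brings 242 back almost exactly, and an article may leave such inputs to the full protocol. This stands as an explanation of where 242 may come from. A reader might infer from the 59% that 80% power is definitely not delivered. The documents do not support that, because they do not say that 0.2 is standardised on the 12-month total.

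The reply does not close the gap with the 40% reduction. The 40% and the 47 (SD 83) are printed as the planning basis, and the SD can belong only to a long-window total. On that total, quarterly recording of the same days adds no information to a time-averaged comparison.

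A second reply is that the 70% rests on a common SD, which the protocol does not state. This also stands. For a skewed count whose mean falls from 47 to 28.2, a smaller SD is reasonable, and power is then about 79% to 85%. A flat statement that the trial has a 30 to 40% chance of missing its assumed effect would therefore go too far.

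Two further inferences should be resisted. The 268 is not an error: 242 / 0.9 = 268.9, and the difference is rounding. Nor is the 10% dropout figure: the 20% is disclosed and the measures meant to reduce it are described. The 20% serves here only as a sensitivity case.

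**Conclusion.** The point holds as an inconsistency in the stated basis. The 242 per group does not follow from the inputs printed with it (394 at d = 0.2; 307 for 40% of 47 days with common SD 83). It needs a repeated-measures reading whose occasions and correlation are not given, and whose 0.2 is not tied to the 40% reduction. On the only scale the paragraph quantifies, 242 per group gives 80% power for about 21 days, a 45% reduction.

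Power for the assumed 40% lies between about 70% and 85%, depending on how the SD changes with the mean, and between about 65% and 81% at 20% loss. These figures assume a two-group comparison of one total per patient, days counted within the reference window, and the quoted SD for the control group. Whether true power is below 80% cannot be settled from the document.

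**What to change.** Keep 268 per group and rewrite the sample-size paragraph in one of two ways.

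- **On the 12-month total:** state that 242 analysed per group gives 80% power for a difference of 0.255 SD (about 21 days, 45%, with a common SD of 83). State also that power for the 40% reduction is about 70%, 79% or 85% under the three SD assumptions, with the values at 20% loss alongside.
- **On the repeated-measures basis:** state the number of occasions, the within-patient correlation and the outcome scale behind 242, and show how an effect of 0.2 on that scale relates to a 40% reduction in inpatient days.

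In either case, replace the conditional baseline adjustment in the Statistical analysis section with a primary model that always adjusts for the inpatient days recorded at t0. These data are already collected. Under a common SD this restores 80% power for the 40% effect if their correlation with 12-month days is at least 0.46. The documents do not give that correlation, so the gain should be shown over a range. It also avoids deciding on adjustment after testing for baseline differences, which matters in a non-randomised comparison.

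The cost is a less favourable stated power, some rewording and a little more analysis work. No extra patients or assessments are needed.

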•Care is provided on the basis of an evidence-informed treatment pathway. This treatment pathway was developed by psychiatrists participating in the intervention. The treatment pathway is based on the German national guideline for Schizophrenia. It considers regional conditions as well as prior experiences with integrated care concepts. The treatment-pathway defines precisely the interaction between the nursing service and the psychiatrist, but also when and how to involve other services such as social services (that have different cost-carriers and budgets than the medical services), rehabilitation services, or inpatient psychiatric care. The treatment pathway is binding for service providers that participate in the AO model. It provides also the basis for reimbursement of services within the AO-model. Thus for purposes of reimbursement service provision in relation to the treatment pathway is continuously monitored.

**Table 1 T1:** Comparison of service provision in “classic” assertive outreach, assertive outreach as implemented in Lower Saxony and treatment as usual (TAU) in mental health care in Lower Saxony and Germany

**Characteristics of service**	**“Classic ” assertive outreach according to DACT-Scale***	**Assertive outreach in Lower Saxony**	**Treatment as usual (TAU) in Lower Saxony/Germany**
Target population	Patients suffering Severe Mental Illness (SMI), high users of mental health services	Patients diagnosed with Schizophrenia	Patients diagnosed with any mental illness
Involved service providers	Multiprofessional: Psychiatrist, nurse and others	Office based psychiatrist in cooperation with specifically trained psychiatric nurse. Further professionals such as rehabilitation specialists are involved as needed. Their involvement is brokered by nurse (case management)	Office based psychiatrist and other services providers as needed (and if available). No standardized pathways for cooperation and exchange between service providers are implemented.
Home treatment	yes	yes	no
Case management	yes	yes	no
Interdisciplinary treatment conferences	yes	yes (usually involving psychiatrist and nurse), meeting once a week	no
Responsible for medical and social needs	yes	yes	no
24/7-service	yes	yes	no
Maximum frequency of contact	high	high	medium
duration of relation	longterm	longterm	longterm

*Dartmouth assertive community treatment scale
[13].

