### Non-response

Even in case of low rates of non-response, patients who are lost to follow-up represent a potential source of selection bias. Therefore we will present a flow chart containing the numbers of patients in different stages of the study (e.g. screened for eligibility, allocated, follow-up) and report reasons for non-response. Furthermore, we will compare baseline characteristics of non-responders and study participants (age, gender and assessment of functioning) as well as of those who are lost to follow-up and those who retain.

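### The only stated response to a missed assessment does not collect admissions or inpatient days, so the primary outcome risks going missing because of the outcome itself

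*Protocol article*

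**What the plan says.** **Missed visits.** Methods, Sample size, cites earlier experience: "Previous studies have shown that 20% of patients cannot be traced for follow-up or do not return questionnaires over a 12-month survey period". To improve on this, practices keep "telephone contact details as well as secondary contact names and addresses at the practices of the attending psychiatrists". Patients who do not return are phoned: "they are contacted by phone and asked whether they want to continue with the study". On that basis "we hope to keep the number of drop-outs at a rate of 10" per cent, and the target "will be 268 patients per group or 536 in total" follows. No arm-specific drop-out rate is given.

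**Source of the primary outcome.** Hypotheses I and II (Background) concern admissions and inpatient days. Under Outcome and process parameters, both come from the Client Sociodemographic and Service Receipt Inventory (CSSRI), which asks the patient about the past three months and is given five times in both groups. The Discussion (Researching a real life implemented intervention) says the practice assistant completes it together with the patient. Under Ethics and dissemination, researchers have no direct contact with patients. No hospital, insurer or practice-record source is named.

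**Setting in each arm.** The Background gives each AO patient a personal nurse case manager, home treatment and a 24/7 crisis service. Table 1 enters no for all three under TAU and adds: "No standardized pathways for cooperation and exchange between service providers are implemented".

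**Reporting of loss.** Methods, Non-response, acknowledges selection bias. It plans a flow chart and reasons for non-response, and states: "we will compare baseline characteristics of non-responders and study participants (age, gender and assessment of functioning"). It also plans to compare those lost with those retained. Statistical analysis adds a per-protocol analysis of completers, an intention-to-treat approach that takes drop-outs into account, and analysis of missing data.

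**The concern.** The outcome is time in psychiatric hospital, and a patient in hospital cannot easily attend the practice. A missed assessment is therefore plausibly a consequence of the event being counted. The stated call addresses willingness to stay in the study. It does not, as described, obtain the admissions and days that the missed assessment would have recorded. Because the CSSRI looks back three months, a later visit does not cover a quarter already missed.

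Three groups are exposed: patients who decline, patients who cannot be reached, and patients who return after a missed window. If they have more inpatient days than those retained, Hypotheses I and II are tested on patients with too few days. The shortfall would bias the comparison if it differed between arms. More frequent AO contact makes that possible. In a non-randomised comparison, preventable selection at follow-up would add to whatever selection is present at entry.

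**Working it through.** **1. The plan's own figure.** From "a baseline sample size of 242 participants in each group" and 10% drop-out: 242 / (1 − 0.10) = 268.9, so 269 per group and 538 in total. The stated 268 and 536 agree to within rounding (268 × 0.90 = 241.2). If loss were the cited 20%, 268 × 0.80 = 214 per group would remain, and 242 / 0.80 = 302.5, so 303 per group would be needed. The recruitment target therefore depends on the tracing measures working.

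**2. Inputs for the illustration.**
- From Sample size: mean 47 inpatient days and an expected reduction of 40%. The planned difference is 0.40 × 47 = 18.8 days, and the AO mean under that effect is 47 − 18.8 = 28.2.
- Assumed, not in the document: patients lost have k times their arm's mean days, with k = 2 as the central value and 1.5 to 3 as the range. Unequal loss is taken as 5% in one arm and 15% in the other, which averages the planned 10%. Patients lost contribute no data.

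**3. Formula.** With true arm mean M and loss d, the retained mean is M(1 − dk) / (1 − d).

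**4. No true effect (47 days in both arms), k = 2.**
- 5% loss: (47 − 0.05 × 94) / 0.95 = 42.3 / 0.95 = 44.5.
- 15% loss: (47 − 0.15 × 94) / 0.85 = 32.9 / 0.85 = 38.7.
- The spurious difference is 5.8 days, and 5.8 / 18.8 = 31% of the planned effect. It runs against AO if TAU has the 15% loss and in favour of AO if AO has it.
- For k = 1.5 to 3 the shift is 2.9 to 11.6 days.
- Equal 10% loss gives a difference of 0 for any k.

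**5. Planned effect true (47 and 28.2 days), k = 2.**
- 10% loss in both arms: TAU (47 − 9.4) / 0.90 = 41.8; AO (28.2 − 5.64) / 0.90 = 25.1; difference 16.7 (range over k: 17.8 to 14.6).
- 5% AO, 15% TAU: 38.7 − 26.7 = 12.0 (15.4 to 5.2).
- 15% AO, 5% TAU: 44.5 − 23.2 = 21.3 (20.1 to 23.8).

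**6. Whether the planned reporting would repair this.** The flow chart and the reasons describe who was lost. The baseline variables named are age, gender and functioning; arm and inpatient use at t0 are not among them, although the CSSRI collects service use at t0. The intention-to-treat approach names no source for the later admissions of drop-outs. None of these steps recovers the missing outcome.

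**The case against.** The strongest reply is that the sentence is a retention measure in a condensed article. It does not say that a refusal ends all data collection, and patients who agree to continue can still be assessed. Call scripts and withdrawal levels often sit in a full protocol or consent form that is not shown. This stands, and it confines the point to patients who decline or cannot be reached and to windows already missed. The gap remains in the text as written, because the only stated outcome source needs the patient and the only stated missed-visit action does not use the call to obtain the outcome.

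A reader might infer that admissions are in fact lost more often under TAU because AO staff know where their patients are. The document does not support that. The missed-visit rule, the secondary contacts, the collector, the schedule and the honoraria are the same in both arms, and both arms are recruited from the same psychiatrists. No AO nurse is given a role in tracing or data collection. Unequal loss is plausible but not shown.

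Nor does the text support the inference that deaths or long admissions would simply be recorded as drop-out, since reasons for non-response are to be reported.

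The illustration is also a simplification. Service use is collected five times and repeated-measures models are planned, so quarters completed before loss can still contribute, and the true distortion may be smaller. Finally, a fallback on practice records could itself find admissions unequally, given what Table 1 says about exchange between providers under TAU. The fix has to allow for that.

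**Conclusion.** The point holds as a risk. As stated, the plan leaves admissions and days uncollected for patients who decline, cannot be reached or are in hospital at an assessment, and the loss is plausibly related to the outcome. Differential loss between arms is an inference, and the direction of any bias is unknown.

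With doubled days in those lost, a 5%/15% split moves the difference by about 5.8 days either way under no effect, nearly a third of the planned 18.8. Equal 10% loss creates no false effect but shrinks a true 18.8 to about 16.7. These figures rest on the assumed loss split, the assumed multiplier and no partial data from those lost; only the 47 days, the 40% and the 10% come from the article. The change is worth making because it is cheap and missed three-month windows are hard to recover later.

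**What to change.** Apply the same changes in both arms.

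1. **Sample size, missed-visit rule.** At the call already planned, complete the CSSRI inpatient items by phone, covering the whole period since the last completed assessment.
2. **Consent.** Separate stopping questionnaires from withdrawing outcome data. Ask at consent to keep admissions, inpatient days and vital status to month 12. Where the patient cannot be reached, use the practice's information only as a flagged fallback, with a sensitivity analysis that excludes it, because TAU records may capture admissions less completely.
3. **Non-response.** Report loss by arm. Compare lost and retained patients within each arm, adding inpatient days and admissions at t0. List death and current hospitalisation among the reasons.

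The cost is one consent line, settled before enrolment, a short phone form for the practice assistant, a few minutes per missed visit and a wider attrition table. The drawback is that some outcomes will come from mixed sources.

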### Non-response

Even in case of low rates of non-response, patients who are lost to follow-up represent a potential source of selection bias. Therefore we will present a flow chart containing the numbers of patients in different stages of the study (e.g. screened for eligibility, allocated, follow-up) and report reasons for non-response. Furthermore, we will compare baseline characteristics of non-responders and study participants (age, gender and assessment of functioning) as well as of those who are lost to follow-up and those who retain.

### Statistical analysis

We will analyse data using per-protocol analysis, considering only those patients who successfully completed the study, as well as using an intention-to-treat approach. Thereby we would also consider those patients who dropped out of the study or changed their originally allocated group.

We will report baseline demographic and clinical characteristics for each study condition and test for baseline equivalence using parametric and non-parametric test as appropriate. If necessary, we will control for baseline differences. Missing data will be analysed.

Longitudinal data will be analysed using standard models for repeated measures including multivariate mixed effects analysis of variance, random effects and generalized estimating equation (GEE) models, as appropriate.

Whenever possible, measures of "practical relevance" such as proportion of explained variance, accuracy of prediction, or effect size will be reported. Statistical analyses will be performed using standard software packages (SPSS, STATA).

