### Recruitment

Patients will be recruited in the practices of office-based psychiatrists who provide AO. Recruitment will be done by the treating psychiatrist. Unfortunately, we were not successful in convincing the attending psychiatrists to support “real” randomisation of patients receiving AO or those receiving TAU. “Real” randomisation would have meant that the office-based psychiatrists would lose 50% of the extra money they receive from health insurance companies when providing AO. Therefore, a quasi-experimental design will be used instead. As patients allocated to receive the intervention all those patients are considered, who are insured by a health insurance that reimburses AO, and who in fact receive AO. All patients who - due to their health insurance affiliation - are not eligible for AO are considered to be controls. We assume that the affiliation with a specific statutory health insurance company is more or less random. Choice of health insurance company is free, all statutory health insurance companies offer approximately the same services, cost the same and are obliged to insure people regardless of their health and financial status. Even if there might be some differences in social status between the members of different health insurance companies, these differences are most likely obliterated by the social consequences of suffering from schizophrenia.

In this quasi-experimental design, all attending practices recruit the same number of patients receiving the intervention and of patients being controls. An honorarium of 150€ will be paid to the practice per assessment and patient. Patients will receive an honorarium of 20€ per assessment.

Eligibility criteria are: being at least 18 years of age, suffering from schizophrenia (ICD-10 F 20) as diagnosed clinically by the treating psychiatrist, having a maximum score of 60 on the Global Assessment of Functioning Scale (GAF)
[14] and being cognitively and linguistically able to fill out the patient questionnaire.

Recruitment is planned to take a year.

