### Bias

We aim to recruit equal numbers of patients receiving the intervention and of controls from the same psychiatrist. Thus, possible bias in respect to context variables will be minimised. Further, the relatively high number of participating psychiatrists should eliminate data distortion due to different physician-patient interaction styles.

The quasi-experimental design that distinguishes participants by their affiliation to a specific health insurance company and thus, their eligibility for AO, can limit the study validity. The data from the study will show whether our assumption is true that schizophrenic patients in different health insurance companies are more or less equal in terms of socio-economic and health status.

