## Endnotes

^a^There are 146 statutory health insurance companies in Germany, insuring approximately 90% of the population. AOK and TK are among the larger health insurance companies. AOK Lower-Saxony insures more than one quarter of the population in Lower-Saxony, TK insures close to one tenth of the population in Germany. While AOK insured traditionally have a lower socioeconomic status, TK insured come from an academic and middle class background. Probable social disparities between the insured populations of health insurances companies are originated in former times, when health insurance affiliation was bound to the workplace. For more than 15 years now, choice of health insurance has been free and social disparities between the insured populations of the health insurance companies are levelling out.

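### Confounder adjustment in this non-randomised comparison is conditional on baseline tests, which miss modest imbalances more often than they find them

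*Protocol article*

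**What the plan says.** The Statistical analysis section of the protocol article says the study will "test for baseline equivalence using parametric and non-parametric test as appropriate. If necessary, we will control for baseline differences". It gives no other criterion for when control is needed, and no section of the article names a set of variables that is always adjusted for. The same section plans repeated-measures models (mixed effects, random effects, GEE).

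The groups are not randomised. Under Recruitment, the intervention group is those "who are insured by a health insurance that reimburses AO, and who in fact receive AO", and "All patients who - due to their health insurance affiliation - are not eligible for AO are considered to be controls". The stand-in for randomisation is an assumption: "We assume that the affiliation with a specific statutory health insurance company is more or less random". The Bias section leaves its confirmation to the results: "The data from the study will show whether our assumption is true". The discussion of researching a real-life intervention accepts that selection bias may impair validity, and the Bias section accepts that the insurer-based design can limit it.

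**The concern.** In a randomised trial, testing baseline differences and then adjusting is poor practice but does little harm, because any imbalance is due to chance. Here systematic imbalance is possible by design. Controls differ from AO patients in insurer, and AO patients are further selected by having consented to AO and received it. The rule then relies on a test that was not sized to find modest imbalances. A variable that fails to reach significance is treated as balanced, its contribution stays in the treatment estimate, and several such contributions in one direction add up. The adjustment set also depends on the data. At stake are the estimates for both main hypotheses, admissions and inpatient days, which could be biased either way.

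**Working it through.** **Inputs from the article (Sample size).** 242 per group before dropout and 268 recruited; two-tailed 5% level; target effect size 0.2; mean 47 inpatient days, SD 83; expected reduction 40%.

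- Recruitment: 242/0.9 = 268.9, in line with the stated 268.
- Target in days: 0.40 × 47 = 18.8 days, or 18.8/83 = 0.227 SD.

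The article states no error rate for the baseline-test rule, so there is no figure of its own to reproduce. Its sample sizes serve here only to set n.

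**Step 1: what the baseline test can see.** For a true imbalance of d SD with n per group, the approximate power of a two-sided 5% test is Φ(d√(n/2) − 1.96). The opposite tail is negligible. With n = 268, √(n/2) = 11.58.

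- d = 0.10: Φ(1.158 − 1.96) = 0.21, so missed about 79% of the time.
- d = 0.15: Φ(1.736 − 1.96) = 0.41, so missed about 59%.
- d = 0.20: Φ(2.315 − 1.96) = 0.64, so missed about 36%.

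**Step 2: what this does to the treatment comparison.** This was simulated with 242 per group, no AO effect and a continuous normal outcome. Each baseline confounder is shifted by d SD in one group and enters the regression only if its own t-test gives p < 0.05. The number of confounders, d, the slopes and the 0.05 entry level are assumptions; the article gives none of them. Runs per scenario: 20,000 with one confounder, 10,000 with three, 4,000 with five or six independent ones.

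| Confounders | d (SD) | Standardised slope | Type I error, test-then-adjust | Residual bias (SD) | Type I error, always adjusted |
|---|---|---|---|---|---|
| 1 | 0.10 | 0.3 to 0.5 | 5.3% | 0.017–0.027 | 5.0–5.1% |
| 1 | 0.15 | 0.3 to 0.5 | 5.4–5.9% | 0.018–0.029 | 4.9–5.2% |
| 3, same direction | 0.10 | 0.3 | 7.8% | 0.051 | 5.3% |
| 3, same direction | 0.15 | 0.3 | 8.6% | 0.052 | 5.1% |
| 5–6, independent, same direction | 0.10–0.15 | 0.20–0.25 | 8–17% | 0.056–0.088 | 4–6% |
| 6, intercorrelated at 0.4 | 0.10–0.15 | 0.15 | about 5% | about 0.01 | about 5% |
| 1 or 3, no true imbalance | 0 | 0.3 to 0.5 | 4.6–4.7% | about 0 | about 5% |

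Always adjusting leaves bias of about zero in every row, for measured confounders.

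**Step 3: in days.** At SD 83, the bias is 0.017 × 83 = 1.4 days at the low end of the one-confounder rows, 0.052 × 83 = 4.3 days with three, and 0.088 × 83 = 7.3 days at the top of the range, against a target of 18.8 days.

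**Step 4: sensitivity.** With five or six independent same-direction confounders and follow-up days alone as outcome, a separate run of 3,000 simulations gave 9–18%. Using the baseline outcome as a covariate lowered this to 6.4–8.6%. Analysing change from baseline, when the confounders act equally at both times, gave 4.8–5.3%. Splitting six imbalances four against two gave 6.3%.

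**The case against.** The case on the other side has real substance.

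- **No threshold is stated.** A reader might infer that a variable is dropped whenever its p-value exceeds 0.05. The article names neither that cut-off nor any other. What stands is that the tests come first, adjustment is conditional, and no other trigger is offered. This is a stated rule, not a detail left to a fuller plan.
- **The Endnotes do not show imbalance between the groups.** The statement that "While AOK insured traditionally have a lower socioeconomic status, TK insured come from an academic and middle class background" tempts one to read it as evidence of a difference between AO patients and controls. The Background says both insurers have contracted for AO, so that contrast lies within the intervention group and could partly cancel. The same note says disparities are levelling out. The better grounds are selection by actual receipt of AO and the article's own acceptance of possible selection bias.
- **Baseline inpatient use may already be in the model.** Service use is recorded at t0 and every three months, and repeated-measures models are planned. The article therefore does not support the claim that prior inpatient days are discarded, or that a set amount of power is lost against a follow-up-only analysis. Such models need not cover functioning, symptoms or social status.
- **Adjustment is not the only safeguard.** Equal recruitment of both groups within practices and a common GAF ceiling also help. Neither balances patient-level prognosis within a practice.
- **The size depends on assumptions.** This stands in full, as the last rows of the table and Step 4 show.

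**Conclusion.** The point holds. The article makes confounder control conditional on tests that miss imbalances of 0.10–0.15 SD more often than they find them, in a design where such imbalances cannot be ruled out. That follows from the article's own sample size and a two-sided 5% test.

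The consequence for the treatment comparison depends on assumptions. For true imbalances of 0.10–0.15 SD, the type I error is about 5–6% with one confounder, 8–9% with three, and up to 8–17% with five or six independent confounders acting together, with residual bias of about 0.01–0.09 SD. Inflation is near nil with strongly intercorrelated confounders or no true imbalance, and smaller when the model includes baseline inpatient use. A reader might take the top of that range, about 7 days or over a third of the target effect (7.3/18.8 = 39%), as the expected harm. The documents do not support that; it is a worst case among assumed scenarios.

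The remedy does not depend on which scenario is true: always adjusting kept the error near 5% in all of them.

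**What to change.** Replace the two test-then-adjust sentences with wording such as: *The primary analysis of admissions and inpatient days is a regression model that adjusts, whatever the observed baseline differences, for prior inpatient use, GAF, BPRS, age, gender and one socioeconomic measure from the CSSRI, all recorded at t0, and that accounts for practice. Baseline comparability is described by standardised differences, without significance tests. The unadjusted estimate is reported as secondary.*

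Keep the set short and fix it before outcome data are seen. Account for practice in the regression model rather than by weighting within practices: if all of the roughly 40 practices join, each holds about 536/40 = 13 patients, too few for that.

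The cost is analysis wording and a few degrees of freedom. GAF, BPRS and the CSSRI are already assessed at t0, and age and gender are already planned for the non-response comparison. Two limits should be stated with the change. Unmeasured confounding remains. The t0 clinical variables are valid confounders only if measured before AO starts, which the article does not say, so the timing of t0 relative to the start of AO should be made explicit.
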